## Methods

### Study design

A four-arm randomized controlled clinical trial with four follow-up assessments (immediately before discharge from hospital, 3 months, 6 months and 12 months after discharge) will be carried out in order to test the following primary hypotheses/outcomes: 1) a modified disease-related expressive writing intervention is effective in enhancing physical and psychological health outcomes (HRQoL, anxiety and depression symptoms, medical visits for CVD-related morbidities) relative to a sham condition in which patients write solely about the facts of their experience with CVD and relative to a control empty condition; 2) the modified disease-related expressive writing intervention is more effective in enhancing physical and psychological health outcomes than a standard expressive writing condition in which patients write about the their deepest thoughts and feelings about the most traumatic or negative event they have experienced in their life. Further hypotheses/outcomes concern post-traumatic growth and are: 1) the modified disease-related expressive writing intervention is effective in enhancing post-traumatic growth relative to sham and control conditions; 2) the modified disease-related expressive writing intervention is more effective in enhancing post-traumatic growth than the standard expressive writing task.

Secondary analyses will be conducted in order to explore the relative efficacy of the writing conditions as a function of patients' gender, age, coping styles, negative affectivity and social constraint (type D personality factors), perceived social support and evaluative ratings of the writing intervention. Accordingly, significant interactions between the experimental conditions and the moderator variables mentioned above are postulated such that, for example, patients low on avoidance will benefit more from expressive writing than avoidant patients and that patients perceiving low social support will benefit more than patients perceiving high social support.

The Medical Ethics Committee of Istituto Auxologico Italiano approved the study protocol.

### Study population

#### Recruitment of participants and selection criteria

All coronary patients who will be referred to the S. Giuseppe Hospital of the Istituto Auxologico Italiano for residential cardiac rehabilitation (CR) and who will meet inclusion criteria of having had a medical diagnosis of Coronary Heart Disease (CHD) and being affected by major cardiovascular risk factors will be asked and screened for admission in the study. CHD is defined as a history of at least one of the following conditions: myocardial infarction, coronary artery by-pass grafting (CABG) and coronary angioplasty (PTCA). Patients will not be selected if they will be diagnosed with recent (less than four weeks) myocardial infarction, CABG or PTCA, if they will be unable to read and write in Italian and if they will have an age ≥ 70 years.

### Randomization procedure and blinding

All participants will be randomly assigned to the experimental conditions in a consecutive way. The simple randomization scheme will be generated by using the Web site http://www.randomization.com. Random allocation will take place after the baseline measurements and patients will be blind to condition assignment.

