### Sample size calculation

Given that no study has yet evaluated the health effects of expressive writing on patients with CVD and considering the small mean effect sizes calculated by Frattaroli in her meta-analysis on expressive writing studies [37], no appropriate and reasonable empirical data are available for calculating the necessary sample size that would allow a high chance to detect a significant difference across conditions. Because of this, the study may be considered partially explorative and a very large sample (the one necessary to detect the small effect sizes obtained by Frattaroli in her meta-analysis) is thus not needed. Hence, calculations were based on the explorative assumption that the effect of expressive writing on coronary patients' health-related quality of life is large (f = 0.4) in accordance to Cohen's classification [38]. We further decided not to make assumptions on sidedness because the expressive writing procedure may also have negative effects in comparison with the control empty group. On the basis of such considerations, a total sample of 92 participants (n = 23 for each condition) is required taking into account a total dropout rate of 20% to detect this large difference with an alpha of 0.05 two-sided and a power of 0.82. Calculations were made with SamplePower (Release 2.0; SPSS, Inc., Chicago, IL).

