Participants will be randomized to one of the following four conditions: 1) disease-related expressive writing (DS-EW); 2) standard expressive writing (S-EW); 3) unemotional writing (Sham) and 4) an empty condition not involving a writing task (assessments only). All the active conditions (1, 2 and 3) will consist in four 20-minute writing sessions that will occur during the hospital stay within a 2-week period and that will be scheduled twice a week for each participant.

Writing instructions for the three active groups will be as follows:

At the end of the CR program and before discharge, all participants, including those assigned to the empty control condition, will be re-administered the outcome questionnaires and will be told that they will receive other follow-up questionnaires by mail at 3, 6, 9 and 12 months after discharge from hospital. A form on which to record any medical visits or events over the previous 3 months will be also sent at each participant at each follow-up assessment.

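### Simple randomisation does not ensure the planned 23 patients per condition; the average loss of power is about 1 point, with a larger but avoidable loss in unlucky allocations

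*Protocol article*

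**What the plan says.** Under Randomization procedure and blinding, the protocol states that "All participants will be randomly assigned to the experimental conditions in a consecutive way" and that "The simple randomization scheme will be generated by using the Web site" of a named online service. It mentions no blocking, stratification or fixed total per arm. Allocation follows the baseline measurements.

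Under Experimental and clinical protocol there are four conditions: disease-related expressive writing (DS-EW), standard expressive writing, unemotional writing (sham) and an empty control.

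Under Sample size calculation, "a total sample of 92 participants (n = 23 for each condition) is required". That figure already includes an allowance for 20% dropout. The calculation assumes a large effect, f = 0.4, "with an alpha of 0.05 two-sided and a power of 0.82".

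Under Study design, the primary hypotheses compare DS-EW with sham, with the empty control and with standard expressive writing. No power is stated for these pairwise contrasts.

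**The concern.** Simple randomisation is the usual term for independent, unrestricted assignment of each patient. Under it, 23 per condition is an average over possible lists and not a property of the list the trial will use. The two sections therefore do not fit together: one plans fixed, equal arms and the other chooses a method that does not deliver them.

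What is at stake is precision. DS-EW is common to all three primary comparisons, so a small DS-EW arm weakens all of them at once. The trial is small, is sized on an assumed large effect and has little power to spare.

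**Working it through.** **Inputs.** From the protocol: N = 92, four arms, 23 per arm, 20% dropout, f = 0.4, alpha 0.05 two-sided, power 0.82. Assumed: probability 1/4 per arm (implied by equal planned sizes) and dropout that is random and independent of arm.

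**1. The plan's own figure.** For the one-way four-group F test, the noncentrality is λ = N f², with 3 and N − 4 degrees of freedom.
- With 19 completers per arm, N = 76 and λ = 76 × 0.16 = 12.16. Power is 0.823, which matches the stated 0.82.
- 76 × 1.2 = 91.2, or 19 × 1.2 = 22.8 per arm, which rounds up to 23 per arm and 92 in total.
- The stated power therefore rests on about 19 completers per arm. The 23 is the enrolment figure.
- Taken literally, 20% dropout from 92 leaves 73.6 completers (18.4 per arm) and power 0.809. Dividing by 0.8 would have given 76 / 0.8 = 95. This is a small side point.

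**2. Arm sizes under simple randomisation, before dropout.**
- SD of one arm = √(92 × 0.25 × 0.75) = 4.15.
- P(23, 23, 23, 23) = 92! / [(23!)⁴ × 4⁹²] = 0.0011, or 0.11%.
- By simulation (multinomial, 1,000,000 draws), the expected smallest arm is 18.2 and the expected largest 28.0. The median gap between them is 9.

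| Event | Smallest of the four arms | DS-EW (one named arm) |
|---|---|---|
| 18 or fewer | 51% | 14% |
| 15 or fewer | 12% | 3% |

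The first column is simulated. The second is the exact binomial(92, 1/4) probability.

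**3. Effect size for a pairwise contrast.** The protocol gives only f. If DS-EW alone differs by d from three equal arms, f = d × √(1/4 × 3/4), so d = 0.4 / √(3/16) = 0.924. This is one assumed pattern of means; others give a different d.

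**4. Power after dropout.** Each patient completes with probability 0.8, under both schemes. Power comes from the noncentral F (four groups) or noncentral t (pairwise) distribution, evaluated over the simulated arm sizes, with only DS-EW differing.

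| Test | Quantity | 23 per arm allocated | Simple randomisation | Loss (points) |
|---|---|---|---|---|
| Four-group F | mean | 0.805 | 0.795 | 1.0 |
| Four-group F | 5th percentile | 0.738 | 0.663 | 7.5 |
| Pairwise, d = 0.924 | mean | 0.773 | 0.760 | 1.3 |
| Pairwise, d = 0.924 | 5th percentile | 0.713 | 0.651 | 6.2 |

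For other patterns of means giving f = 0.4, mean power of the F test under simple randomisation lies between 0.795 and 0.802.

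**5. How much of the contrasts' weakness is due to allocation.** Here each arm keeps exactly 80% of its patients. At d = 0.8 (assumed), pairwise power is 0.655 with perfect balance and 0.643 on average under simple randomisation. At d = 0.5 (assumed) the figures are 0.314 and 0.308. Most of the shortfall comes from sizing the trial on the overall test; allocation adds about 1 point.

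**The case against.** Simple randomisation is valid, unbiased and fully unpredictable, and preferring blocks to it is partly a matter of taste. Unpredictability has some value here: a research investigator approaches and screens the patients, and the investigator who codes the medical visits knows the assignments. With four arms, the last assignment in a block of 4 can be deduced once the block is recognised. Random dropout would unbalance the analysed arms under any scheme, and the protocol calls the study partly exploratory. All of this stands. It limits the size of the point but does not reconcile the two sections.

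Three stronger readings are tempting, and the documents do not support them.
- A reader might infer that one arm will often be far too small for its contrasts. The 51% refers to whichever arm is smallest; for DS-EW the figure is 14%, and the average cost is about 1 point of power.
- A reader might infer that the stated power collapses because it needs exactly 23 in each arm. It reproduces with about 19 completers per arm, so the 0.11% chance of exact balance says nothing about its validity.
- A reader might infer that consecutive enrolment lets arm sizes drift over calendar time and so biases the comparison. Under simple randomisation assignment is independent of enrolment time, so chance drift brings no bias.

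The word simple may also have been used loosely for a restricted list. Nothing in the text indicates this, and if it is so, the description itself needs correcting.

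**Conclusion.** The point holds as an inconsistency with a modest cost in efficiency: the stated method does not secure the stated number per condition. The average loss of about 1 point, for the overall test and for a pairwise contrast, would not by itself change any conclusion. The loss of about 6 to 8 points at the 5th percentile is worth removing because it can be avoided so cheaply. These sizes assume equal allocation probabilities, 20% random dropout and, for the 5th-percentile figures, that only DS-EW differs (d = 0.92). The validity of the comparison is not in question.

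**What to change.** Generate the list with permuted blocks of randomly varying size, for example 4 and 8, with equal allocation to the four conditions. Keep the block sizes and the list from the investigator who recruits, and release each assignment only after baseline, as the protocol already intends. State the method in the randomisation section. If the list already generated was restricted, correct that section to say so.

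The cost is a different list and a sentence of text. The one downside is slight predictability, which varying and undisclosed block sizes keep small. The change restores the planned allocation to within an incomplete final block and removes most of the tail risk. It does not cure the low power of the pairwise contrasts, which has a different cause.

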### Sample size calculation

Given that no study has yet evaluated the health effects of expressive writing on patients with CVD and considering the small mean effect sizes calculated by Frattaroli in her meta-analysis on expressive writing studies [37], no appropriate and reasonable empirical data are available for calculating the necessary sample size that would allow a high chance to detect a significant difference across conditions. Because of this, the study may be considered partially explorative and a very large sample (the one necessary to detect the small effect sizes obtained by Frattaroli in her meta-analysis) is thus not needed. Hence, calculations were based on the explorative assumption that the effect of expressive writing on coronary patients' health-related quality of life is large (f = 0.4) in accordance to Cohen's classification [38]. We further decided not to make assumptions on sidedness because the expressive writing procedure may also have negative effects in comparison with the control empty group. On the basis of such considerations, a total sample of 92 participants (n = 23 for each condition) is required taking into account a total dropout rate of 20% to detect this large difference with an alpha of 0.05 two-sided and a power of 0.82. Calculations were made with SamplePower (Release 2.0; SPSS, Inc., Chicago, IL).

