A recent special issue of the British Journal of Health Psychology edited by Joshua Smyth and James Pennebaker [11] confirms the breath of current interest in the expressive writing paradigm and invites to look forward at the many remaining frontiers in Expressive Writing research. One of the boundary conditions that have been identified in their commentary paper concerns new outcome measures and previously unexamined populations. Surprisingly, the expressive writing procedure has never been used with patients with CVD. Perhaps, clinical researchers have been negatively impressed by some negative results [12]. Furthermore, in a review on the putative theories underlying the expressive writing procedure, Sloan and Marx concluded that it was too early to say definitively whether expressive writing is a trustworthy technique that should be adopted by the therapeutic community [13]. However, the meta-analysis by Frisina, Borod and Lepore [14] on 9 writings studies using clinical populations showed that expressive writing significantly improved health outcomes (d = .19) and the strongest effect was found for physical health outcomes (d = .21). Moreover, the expressive writing procedure is tremendously cost-effective, easy to administrate, feasible and brief, does not need highly trained clinicians to work, has a great accessibility and has shown an amount of promising objective and subjective health benefits in many studies on college students and individuals from the community. Such appealing features have made it very attractive for some clinicians and clinical researchers who, beginning in the 90s and going on until nowadays, have started to use the expressive writing procedure with their patients and to examine its effects empirically in many randomized clinical trials involving individuals with physical disorders such as breast cancer [15-18], rheumatoid arthritis [19], fibromyalgia [20], HIV [21,22], renal cell carcinoma [23], men diagnosed with prostate cancer [24], women with chronic pelvic pain [25], men with elevated blood pressure [26], patients undergoing bladder papilloma resection [27] and transurethral prostate resection [28].

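### The stated power of 0.82 belongs to an omnibus four-arm comparison with 19 evaluable per arm; it does not apply to the pairwise primary hypotheses, and 92 enrolled less 20% falls slightly short of it

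*Protocol article*

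**What the plan says.** The sample size section of the protocol article assumes that the effect on "health-related quality of life is large (f = 0.4"). It states that "a total sample of 92 participants (n = 23 for each condition) is required taking into account a total dropout rate of 20" per cent, "to detect this large difference with an alpha of 0.05 two-sided and a power of 0.82". The target is described as a difference across conditions, and no test is named. The same section calls the study partially explorative and says it is not sized for the small effects found in meta-analysis.

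The Study design section states the primary hypotheses as specific comparisons. Hypothesis 1 sets disease-related writing against the sham condition and against the empty control. Hypothesis 2 is that "the modified disease-related expressive writing intervention is more effective in enhancing physical and psychological health outcomes than a standard expressive writing condition". The Statistical analysis section tests the hypotheses as interactions between time and condition in a multilevel model, at alpha 0.05. No power is given for any single comparison or for the interaction.

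**The concern.** Cohen's f for four groups measures the overall spread of four means. Power computed on that scale is the chance of concluding that the arms differ somehow. A significant overall test establishes none of the named comparisons, so a power figure for it cannot be carried over to them. There is also a smaller arithmetic question: whether 92 enrolled, after the stated dropout, leaves the number that gives 0.82.

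What is at stake is how the result will be read. A non-significant comparison of disease-related writing with sham or with standard writing could be taken as coming from a trial with 82% power for that comparison, and nothing in the article supports that.

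**Working it through.** **Inputs (sample size section).** f = 0.4; four equal arms; alpha 0.05 two-sided; power 0.82; 92 enrolled, 23 per arm; 20% total dropout.

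**Step 1: reproduce 0.82.** For a one-way omnibus F test with k = 4 and n per arm, the numerator df is 3, the denominator df is 4n − 4, and the noncentrality is λ = 4n·f² = 0.64n.

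| n per arm | λ | Power |
|---|---|---|
| 18 | 11.52 | 0.799 |
| 18.4 | 11.78 | 0.809 |
| 19 | 12.16 | 0.823 |
| 23 | 14.72 | 0.898 |

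The stated 0.82 matches 19 evaluable per arm. At the full 23 it would be 0.90, so 0.82 is a post-dropout figure. Three things point to the omnibus test: the f scale, the description of a difference across conditions, and the match at 19.

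**Step 2: dropout.** 19 × 1.2 = 22.8, rounded up to 23, and 4 × 23 = 92. To keep 19 after losing 20% requires 19/0.8 = 23.75, so 24 per arm (96 in total). From 92, 92 × 0.8 = 73.6 remain, or 18.4 per arm. Power is then 0.809, or 0.799 with 18 whole patients per arm. The shortfall is 1 to 2 percentage points.

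**Step 3: the named contrasts, as a single-time-point illustration.** The article gives no pattern of means, so several patterns with f = 0.4 are shown. If one arm differs from three, δ·√3/4 = 0.4, so δ = 0.92 SD. If two arms differ from two, δ/2 = 0.4, so δ = 0.80. If the means are equally spaced, step·√5/2 = 0.4, so the step is 0.358. Power comes from a two-sided t test at 0.05 with 18 per arm, pooled error df 68 and noncentrality d·√(18/2) = 3d. Joint figures come from simulation (200,000 runs).

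| Pattern | vs standard | vs sham | vs empty | Both parts of hypothesis 1 | All three |
|---|---|---|---|---|---|
| Only disease-related arm differs (d = 0.92) | 0.78 | 0.78 | 0.78 | 0.66 | 0.59 |
| Graded (d = 0.48, 0.96, 0.96) | 0.30 | 0.81 | 0.81 | 0.71 | 0.27 |
| Both expressive arms above both controls (d = 0, 0.8, 0.8) | no difference | 0.66 | 0.66 | 0.51 | not applicable |
| Equally spaced (d = 0.36, 0.72, 1.07) | 0.18–0.19 | 0.56 | 0.89 | 0.54 | 0.15 |
| Two extremes (d = 0.57, 0.57, 1.13) | 0.39 | 0.39 | 0.92 | 0.38 | 0.23 |

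**Step 4: what one contrast can detect.** At 18 per arm, 80% power needs d of about 0.95 (0.947 with pooled df, 0.961 with two-sample df). The Study rationale section cites a meta-analysis in clinical populations in which "expressive writing significantly improved health outcomes (d = .19"), with .21 for physical health. At d = .19 to .21 the power is 0.086 to 0.095, about 9%.

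**The case against.** *The dropout slip is trivial.* This stands. At the stated 20% loss, power is 0.81 against 0.82, and a multilevel model can use partial follow-up, so a dropout need not be a wholly lost patient. Alone, the slip would not justify revising the text.

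*Some contrasts do reach 0.82.* This also stands. A reader might infer that every named comparison has less than the stated power under f = 0.4. The figures do not support that: the largest contrast has 0.89 with equally spaced means and 0.92 with two extreme means. What fell short in every pattern tried is joint success on hypothesis 1 or on all three contrasts.

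*The pairwise figures are not for the planned analysis.* Correct. Repeated measurements could raise power; a test of slopes could raise or lower it. The article gives no within-person correlations or slope variances, so the figures in the working are an illustration and not the trial's power. By the same token, nothing in the article supports 0.82 for the planned test.

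*The study is openly exploratory.* A reader might infer a contradiction between citing effects near 0.2 in the rationale and sizing for a large effect. There is none. The sample size section says that meta-analytic effects are small, that detecting them would take a very large sample, that no data exist in cardiovascular patients, and that f = 0.4 is an exploratory assumption. The remark that a very large sample is not needed can stay. The exploratory label does not, however, attach 0.82 to hypotheses that the article calls primary and tests at 0.05.

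**Conclusion.** The power statement is wrong as written, in two unequal ways. The minor one: after 20% loss from 92, power for the overall four-arm comparison at f = 0.4 is 0.80 to 0.81, not 0.82. The material one: the figure describes a different test from the primary hypotheses and from the planned time-by-condition analysis.

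This rests on the inference that the calculation was a one-way omnibus test. The per-contrast figures rest further on a single time point, 18 evaluable per arm, equal variances, no multiplicity adjustment, and assumed patterns of means. Power for the planned multilevel interaction cannot be computed from the article. The point should be fixed, but it does not call the sample size or the design into question.

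**What to change.** Keep 92 participants and restate the sample size section to say that:

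- 0.80–0.81 is the power of the omnibus four-group comparison at f = 0.4 after 20% loss (about 18 per arm).
- This is not the power for the pairwise primary hypotheses or for the time-by-condition test.
- At a single time point, ignoring repeated measures, a pairwise contrast has 80% power for d of about 0.95 and about 9% power at the d = .19 to .21 cited in the rationale.
- Power for the planned multilevel interaction depends on within-person correlations and slope variances that are not given.

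The cost is wording only: no extra patients and no change to design or analysis. The one downside is that a stated figure becomes less favourable.
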